**Hypothesis**

Based on previous studies conducted by different research groups, in laboratory and field settings, we hypothesize that the use of therapeutic resources will favor muscle recovery optimization in Cross Training athletes after the completion of a WOD, which is considered a strenuous exercise.

**Objectives**

**General Objective:**

To compare the effects of three different therapeutic resources—PBMT-sMF, IPC, and ESWT—on muscle recovery in Cross Training participants.

**Specific Objectives:**

- To analyze the effects of therapeutic resources on performance-related variables by assessing muscle recovery capacity through functional evaluation.
- To evaluate the effects of therapeutic resources on biochemical markers related to muscle recovery and oxidative stress.

**METHODS**

**Study Design and Ethics**

This randomized, controlled, crossover clinical trial with blinded outcome assessors will be prospectively registered at ClinicalTrials.gov. The study will be submitted to the Ethics Committee of Universidade Nove de Julho and conducted in accordance with the Declaration of Helsinki. Written informed consent will be obtained.

**Participants**

The trial will be conducted in São José dos Campos, Brazil. Healthy male amateur Cross Training athletes aged between 18 and 35 years, who have been training at least four times per week for a minimum of one year, will be included. Exclusion criteria will include pharmacological use or recent musculoskeletal injuries. In addition, individuals who sustain musculoskeletal or joint injuries during the study will also be excluded.

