According to Claudino et al. (2018), Cross Training is considered an excellent option of HIIT (High-Intensity Interval Training). HIIT is a type of interval training at high intensity that improves both anaerobic and aerobic energy supply systems (Tabata et al., 1996; Zhang et al., 2017). When applied to different sports and in Cross Training competitions, HIIT effectively overloads both anaerobic and aerobic energy systems, resulting in improved athletic performance (Tabata et al., 1997; Jagim et al., 2015). However, Cross Training as a sport differs from HIIT by including gymnastic and weightlifting elements, and by reducing or eliminating rest periods (Meyer et al., 2017; Kliszczewicz et al., 2015). As observed in traditional competitions, the main goal of WODs is to complete a specific number of repetitions and exercises in the shortest possible time (Kliszczewicz et al., 2015). Thus, since athletes are often subjected to several WODs on the same day and on consecutive days of competition, they must cope with fatigue and the resulting muscle recovery demands (Hak et al., 2013).

This high physical demand required in intense exercise has raised concerns in the scientific community, as confirmed by several publications investigating the relationship between Cross Training practice and the risk of injuries (Hak et al., 2013; Weisenthal et al., 2014; Sprey et al., 2016; Summitt et al., 2016; Maté-Muñoz et al., 2017). Weisenthal et al. (2014) concluded that fatigue causes alterations in movement biomechanics, increasing injury risk. According to Hak et al. (2013), in their analysis of the nature and prevalence of injuries in Cross Training practitioners, the loss of technique during extreme fatigue is associated with lumbar spine injuries. Maté-Muñoz et al. (2017) added that many exercises used in Cross Training require advanced technique as well as high sustained power output. Therefore, they can induce considerable fatigue and lead to injuries in subsequent training sessions. The fatigue process leads to a decline in physical performance and, in some cases, to injuries (Andersson et al., 2008; Ispirlidis et al., 2008; Nédélec et al., 2012). Thus, it can be inferred that the risk of injury is closely related to fatigue generated by the high intensity required during WOD performance (Hak et al., 2013; Weisenthal et al., 2014; Maté-Muñoz et al., 2017).

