**Blinding and Randomization**

Outcomes will be assessed by an independent evaluator who will be blinded to group allocation. Intervention sequences will be randomized (1:1:1:1) via www.randomization.org by a researcher not involved in other phases of the study. Each participant will complete all four interventions across weekly sessions with seven-day washout periods. Allocation will be concealed using sealed, numbered, opaque envelopes.

The intervention orders will be:

- Sequence 1: PR → PBMT-sMF → ESWT → IPC
- Sequence 2: PBMT-sMF → ESWT → IPC → PR
- Sequence 3: ESWT → IPC → PR → PBMT-sMF
- Sequence 4: IPC → PR → PBMT-sMF → ESWT

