**Outcomes**

The primary outcome will be the change in performance on the functional test, assessed 1-hour post-WOD. Secondary outcomes will include: change in functional test performance at 24 and 48 hours post-WOD; biochemical markers of muscle damage and oxidative stress; antioxidant activity; subjective perception of exertion (assessed at 1, 24, and 48 hours post-WOD); and satisfaction with the intervention (assessed at 48 hours post-WOD).

- Vertical Jump Performance: Vertical jump performance will be measured using the countermovement jump (CMJ) height test (Balsalobre-Fernández et al., 2015). During the test, participants will stand with feet shoulder-width apart and hands on the hips. They will perform a controlled squat to ~90° of knee flexion followed by an explosive vertical jump. Upon landing, they will flex the hips, knees, and ankles to absorb impact. A smartphone camera, positioned 1.5 m away, will record three maximal-effort CMJ attempts (Balsalobre-Fernández et al., 2015). Jump height will be analyzed using the JumPo 2 app (iOS), the only validated tool available at the time. The highest recorded jump will be used for analysis.
- Muscle Damage and Oxidative Stress Markers: Muscle damage will be assessed via lactate dehydrogenase (LDH) levels (De Oliveira et al., 2017). Oxidative stress and antioxidant activity will be assessed using thiobarbituric acid reactive substances (TBARS), carbonylated proteins, catalase (CAT), and superoxide dismutase (SOD) (Pinto et al., 2022). Blood samples (5 mL) will be drawn from the anterior cubital vein and stored at −80 °C for later analysis. LDH activity will be quantified by spectrophotometry using specific reagent kits (Labtest®, Minas Gerais, Brazil) as an indirect marker of muscle damage. TBARS, carbonylated proteins, CAT, and SOD will be analyzed as biomarkers of oxidative stress and antioxidant defense following previously established spectrophotometric protocols (Pinto et al., 2022). Each biochemical analysis will be conducted in triplicate, and the mean value will be used for statistical interpretation.
- Subjective Perception of Exertion: Perceived exertion will be assessed using the Rate of Perceived Exertion (RPE) scale (Fanchini et al., Weston et al., 2015). Participants will rate effort in two domains:
- RPE-MI (Muscular Intensity): perceived lower-limb fatigue.
- RPE-R (Respiratory Effort): perceived cardiorespiratory fatigue.

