**Statistical Analysis**

To the best of our knowledge, no prior study will have compared PBMT-sMF, IPC, ESWT, and passive recovery in Cross Training athletes. Therefore, sample size will be calculated based on CMJ performance data from the first session, following a previously described method (Pinto et al., 2022). This calculation will be conducted by a blinded researcher and will use percentage changes in CMJ at 1-hour post-WOD (primary outcome). An 80% statistical power (α = 0.05; ANOVA) will be considered, and the WebPower (https://webpower.psychstat.org/models/means03/effectsize.php) and Statistics Kingdom (https://www.statskingdom.com/sample_size_regression.html) tools will be used for the computation.

Statistical analyses will follow the intention-to-treat principle (Elkins, 2015). The statistician will remain blinded to allocation to minimize bias. Data normality will be assessed using the Shapiro–Wilk test. Differences between interventions will be evaluated using repeated-measures ANOVA with Bonferroni post hoc tests. Both absolute values and percentage changes from baseline will be analyzed. Results will be presented as mean ± SD (tables) and mean ± SEM (figures). Fisher’s exact test will be used to compare satisfaction proportions across interventions. Statistical significance will be set at p < 0.05.

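### The rule excluding athletes injured during the study does not separate stopping sessions from removal from the analysis, and as written it conflicts with the intention-to-treat statement

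*Protocol*

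**What the plan says.** The Participants section of the protocol first gives the entry criteria: "Exclusion criteria will include pharmacological use or recent musculoskeletal injuries". A separate sentence then adds that "individuals who sustain musculoskeletal or joint injuries during the study will also be excluded". It uses the same verb for both and does not say from what the injured athlete is excluded.

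Under Blinding and Randomization, the unit randomised is a sequence of four interventions, and "Each participant will complete all four interventions across weekly sessions with seven-day washout periods".

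Under Statistical Analysis, "Statistical analyses will follow the intention-to-treat principle", and "Differences between interventions will be evaluated using repeated-measures ANOVA with Bonferroni post hoc tests". The protocol does not say how an athlete with fewer than four sessions enters that analysis.

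Under Outcomes, "The primary outcome will be the change in performance on the functional test, assessed 1-hour post-WOD".

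On what injury means in this trial, the Background argues that "the risk of injury is closely related to fatigue generated by the high intensity required during WOD performance". It also presents recovery strategies as a way to lower injury risk. The Abstract lists adverse effects among the matters to be investigated.

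**The concern.** Intention-to-treat means that a randomised athlete stays in the comparison whatever happens later. A rule that excludes athletes for a later event does the opposite unless it is confined to further participation. If the rule is applied as written, the result is an analysis of uninjured completers reported under an intention-to-treat label.

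Two things are at stake. The first is information: in a four-period crossover, removing one athlete late in the study discards up to three completed sessions. The second is possible bias: if athletes who recover badly are more likely to be injured, and recovery differs by intervention, those removed are not a random subset. Injuries would also disappear from the record of a trial that says it will look for adverse effects.

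**Working it through.** **1. Can both statements be followed as written?**

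| Step | Protocol section | Content |
|---|---|---|
| a | Blinding and Randomization | A four-session sequence is assigned at random |
| b | Study Sessions and Exercise Protocol | The sessions, each with a fatiguing workout, follow over successive weeks |
| c | Participants | An athlete injured during the study is excluded |
| d | Statistical Analysis | Analyses follow intention-to-treat |

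An injury in any session comes after (a). Under (c) the athlete is out, and under (d) the athlete stays in. The two agree only if (c) means no further sessions while collected data are kept. The protocol does not say that.

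**2. What the planned model does with an incomplete athlete.** Standard repeated-measures ANOVA needs a value in every condition. Take an athlete on Sequence 1 who is injured in the third workout. Passive recovery and PBMT-sMF have been observed and give a direct within-person comparison, but listwise deletion discards both. So even the milder reading of (c) loses completed sessions unless another way of handling them is specified.

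**3. How much could be lost.** The protocol gives no injury rate and no sample size, so it has no figure to reproduce. The injury risk per session, q, is an assumption, taken as constant and independent across sessions.

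- Share of athletes removed over four sessions: 1 − (1 − q)^4
- Completed sessions discarded per randomised athlete: Σ (k − 1)·q·(1 − q)^(k − 1), for k = 1 to 4

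| q (assumed) | Athletes removed | Completed sessions discarded per athlete | As a share of four planned |
|---|---|---|---|
| 1% | 1 − 0.99^4 = 3.9% | 0.0586 | 1.5% |
| 2% | 1 − 0.98^4 = 7.8% | 0.1145 | 2.9% |
| 5% | 1 − 0.95^4 = 18.5% | 0.2664 | 6.7% |

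With an assumed 24 athletes, that is about 0.9, 1.9 and 4.5 athletes.

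**4. Does the loss have a direction?** This was checked by simulating 1,000,000 athletes per scenario. All inputs are assumed: mean CMJ change of −8 points under passive recovery and −5 under each active intervention (a true difference of 3), and between- and within-person SDs of 4 each. The log-odds of injury either did not depend on recovery in that period or rose with poor recovery, by the stated slope per SD of 5.66 (√32). Anyone injured was removed.

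| Injury risk at average recovery | Slope | Athletes removed | Difference, all athletes | Difference, uninjured only |
|---|---|---|---|---|
| 2% | 0 | 7.8% | 3.002 | 3.000 |
| 2% | 1 | 11.8% | 3.000 | 2.955 |
| 5% | 1 | 25.4% | 2.992 | 2.904 |
| 5% | 1.5 | 32.3% | 2.994 | 2.810 |

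Bias is absent when injury is unrelated to recovery. Otherwise the difference shrinks towards zero, by about 0.05 to 0.18 points here.

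**5. Does the trial's timing allow that dependence?** Under Interventions, treatment starts five minutes after the workout. An injury in a workout therefore comes before that session's treatment and can depend only on treatments from earlier weeks, across a seven-day washout. Under Study Sessions and Exercise Protocol, athletes avoid physical activity from 24 h before to 48 h after the workout, so an injury in training later that week comes after that session's last assessment. The simulation lets poor recovery in any of the four periods raise the risk, including the last, which no study workout follows. It is therefore a generous picture of the mechanism.

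**The case against.** The strongest reply is that the Participants section governs participation, whereas the only sentence on the analysis set is the intention-to-treat statement. If excluded means withdrawn from further maximal workouts, nothing conflicts. That reading is possible, and the authors may have intended it. But it has to be supplied by the reader: the rule stands beside the eligibility exclusions, uses the same word, and carries no statement that collected data are kept.

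A second reply is that the protocol does not prescribe listwise deletion and that handling of missing sessions may be set out in a statistical analysis plan not shown here. That is fair. The loss of completed sessions follows from the standard form of the named method and is not stated by the protocol. A separate plan could resolve it, but the wording of the exclusion rule would still need reconciling.

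A reader might go further and infer that the rule amounts to selection on the primary outcome, with the worst recoverers under a particular intervention removed. The documents do not support this. The Background sentence concerns fatigue produced by the workout, which is the same in all four conditions, and treatment comes after it. Dependence on treatment through earlier periods or later training is possible but not shown.

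Finally, a mixed model does not cure everything. If injury depends on recovery that was never observed, the data are not missing at random and some bias remains. That stands as a limit of the remedy.

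**Conclusion.** The point holds as an unresolved conflict in the text. The protocol excludes athletes for an event after randomisation, does not separate stopping sessions from leaving the analysis, and claims intention-to-treat. Followed as written, with the standard form of the named model, it gives a completers analysis under the wrong label. This holds at any injury rate.

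The size of the consequence is unknown. Under assumed risks of 1% to 5% per session, 3.9% to 18.5% of athletes would be lost. In the simulated scenarios an assumed 3-point difference was attenuated by nothing up to about 0.18 points, the latter with almost a third of athletes removed. If injuries are rare, or unrelated to earlier treatment, bias is small or absent. This is a point that should be fixed; it does not by itself undermine the trial.

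**What to change.** - **Reconcile the two sections.** State that stopping sessions after an injury is not exclusion from the analysis. When sessions should stop is a clinical decision and is not judged here. The injury rule should not simply be deleted, because it may be the only stopping rule in the protocol.
- **Define the analysis set.** Include every randomised athlete with all observed periods, whether recorded before or after an injury.
- **Change the model.** Replace repeated-measures ANOVA with a linear mixed model with a random participant effect and fixed terms for intervention and period. It uses incomplete athletes. The period term matters because interventions are no longer balanced over periods once some sessions are missing.
- **Report injuries** by intervention and period, including those that led to stopping.

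The cost is a few sentences and a routine change of model. The small downside is reliance on missing at random, which is generally a weaker assumption than complete-case deletion needs. The change should be made before outcome data are examined, so that the choice of who is analysed cannot depend on the results.

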**Interventions**

All interventions will be applied five minutes after the WOD and will last 30 minutes, except for PBMT-sMF, which will be applied for 32 minutes.

- **Passive Recovery (PR):** Participants will remain at rest in the supine position throughout the intervention period, serving as the control condition (Gill et al., 2006).
- **Intermittent Pneumatic Compression (IPC):** Sequential compression will be performed using pneumatic boots (model 701 RA, Recovery Pump LLC, Concordville, PA, USA), positioned on both lower limbs. The device will apply a pressure of 80–90 mmHg in four inflatable chambers arranged linearly from the feet to the hips. Each chamber will be sequentially inflated for approximately 8 to 12 seconds, followed by a partial deflation period of 15 seconds, with the complete inflation cycle lasting 30 to 40 seconds (Martins et al., 2015).
- **Extracorporeal Shock Wave Therapy (ESWT):** The intervention will be administered using the Shock Wave Therapy BTL-6000 device (BTL Industries Ltd., United Kingdom), according to the manufacturer’s instructions. Each session will involve 2,000 pulses per region (6,000 pulses per lower limb), with an energy flux density of 0.03 mJ/mm², a frequency of 10 Hz, and a pressure of 1.5 bar (Fleckenstein et al., 2017). A 15 mm diameter acoustic wave transmitter will be applied directly to the skin with conductive gel to optimize coupling and energy distribution (Fleckenstein et al., 2017). ESWT will be targeted at the knee extensor/hip flexor muscles (rectus femoris, vastus lateralis, vastus medialis), knee flexor/hip extensor muscles (hamstrings), and plantar flexor muscles (gastrocnemius) in both lower limbs. Application sites and protocol will follow a previous study and manufacturer guidelines to ensure optimal effectiveness (Fleckenstein et al., 2017).
- **Photobiomodulation Therapy Combined with Static Magnetic Field (PBMT-sMF):** This intervention will be performed using a Multi Radiance Medical device (Solon, OH, USA) equipped with a cluster probe that emits a negligible amount of heat (Grandinétti et al., 2015). The device will contain 20 diodes, distributed as follows: four diodes emitting at 905 nm (1.25 mW average power, 50 W peak power per diode), eight diodes emitting at 850 nm (40 mW average power per diode), and eight diodes emitting at 633 nm (25 mW average power per diode). PBMT-sMF will be applied to eight specific sites in both lower limbs, targeting: four sites in the knee extensor/hip flexor muscles (rectus femoris, vastus lateralis, and vastus medialis); three sites in the knee flexor/hip extensor muscles (hamstrings); and one site in the plantar flexor muscles (gastrocnemius). The parameters for PBMT-sMF will be selected based on previous research to ensure consistency and therapeutic effectiveness (Vanin et al., 2018; Pinto et al., 2022; Antonialli et al., 2014). A full list of PBMT-sMF parameters will be provided in Table 1.

Table 1. PBMT-sMF parameters.

|  | Lasers | Red LEDs | Infrared LEDs |
| --- | --- | --- | --- |
| Number of diodes | 4 | 8 | 8 |
| Wavelength (nm) | 905 | 633 | 850 |
| Frequency (Hz) | 250 | 2 | 250 |
| Peak power (W) | 50 | - | - |
| Average optical output (mW)- each | 1.25 | 25 | 40 |
| Power density (mW/cm^2^) - each | 3.91 | 29.41 | 71.23 |
| Energy density (J/cm^2^) - each | 0.50*; 0.44**; 0.44*** | 3.79*; 3.39**; 3.39*** | 9.21*; 8.21**; 8.21*** |
| Dose (J) - each | 0.16*; 0.14**; 0.14*** | 3.22*; 2.88**; 2.88*** | 5.16*; 4.60**; 4.60*** |
| Spot size of diode (cm^2^) - each | 0.32 | 0.85 | 0.56 |
| Magnetic field (mT) | 110 | | |
| Irradiation time per site (sec) | 129*; 115**; 115*** | | |
| Total dose per site (J) | 67.68*; 60.76**; 60.76*** | | |
| Total dose applied per lower limb (J) | 270.72*; 182.28**; 60.76*** | | |
| Aperture of device | 33 | | |
| Application mode | Direct skin contacts and slight pressure | | |

* Knee extensors, ** knee flexors, *** plantar flexors.

**Blinding and Randomization**

Outcomes will be assessed by an independent evaluator who will be blinded to group allocation. Intervention sequences will be randomized (1:1:1:1) via www.randomization.org by a researcher not involved in other phases of the study. Each participant will complete all four interventions across weekly sessions with seven-day washout periods. Allocation will be concealed using sealed, numbered, opaque envelopes.

The intervention orders will be:

- Sequence 1: PR → PBMT-sMF → ESWT → IPC
- Sequence 2: PBMT-sMF → ESWT → IPC → PR
- Sequence 3: ESWT → IPC → PR → PBMT-sMF
- Sequence 4: IPC → PR → PBMT-sMF → ESWT

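### The four sequences are rotations of one order: period is balanced, but differential carryover would be heavily, though not completely, confounded with treatment

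*Protocol*

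**What the plan says.** The Protocol (Blinding and Randomization) fixes these orders, allocated in equal proportions:

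- Sequence 1: "PR → PBMT-sMF → ESWT → IPC"
- "Sequence 2: PBMT-sMF → ESWT → IPC → PR"
- "Sequence 3: ESWT → IPC → PR → PBMT-sMF"
- "Sequence 4: IPC → PR → PBMT-sMF → ESWT"

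On spacing it says: "Each participant will complete all four interventions across weekly sessions with seven-day washout periods". It gives no reason for the length of the washout.

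Other relevant statements, in summary:

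- Study Sessions and Exercise Protocol: assessments are made before and after every WOD, and only the intervention differs between sessions.
- Outcomes: the primary outcome is the change in the functional test (countermovement jump, CMJ) one hour after the WOD.
- Statistical Analysis: interventions are compared by repeated-measures ANOVA with Bonferroni post hoc tests, on absolute values and on percentage change from baseline. No carryover term is named.

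**The concern.** A crossover with four treatments can be balanced in two respects: each treatment appears equally often in each period, and each treatment is preceded equally often by each of the others. The listed square has the first property and lacks the second. If one week's recovery aid alters the response to the next week's WOD, the residual falls on one particular intervention instead of being spread over the other three.

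The control is exposed in the same way. PR is preceded only by IPC, so a residual from IPC would move the control mean and push all three active-versus-control contrasts in the same direction. The comparisons among the active therapies, which the General Objective puts first, are open to the same distortion.

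**Working it through.** The Protocol states no figure on this point, so there is none to reproduce. The check concerns the structure of the design.

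**Inputs.** The four sequences as listed, with equal numbers per sequence. The model has fixed participant, period and treatment effects, with or without an additive first-order carryover. Write lambda_X for the carryover left by intervention X into the next session. Variances are for one participant per sequence, with within-participant error variance sigma².

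**1. Transitions.** Four sequences with three transitions each give 12. Only four ordered pairs occur, three times each: PR then PBMT-sMF, PBMT-sMF then ESWT, ESWT then IPC, IPC then PR. Each intervention occurs once in each period.

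**2. Bias when carryover is omitted.** Each intervention has a predecessor in three of its four occurrences, and it is always the same one. Its mean therefore carries 3/4 of that predecessor's residual:

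bias(i - j) = 0.75 × (lambda of i's predecessor - lambda of j's predecessor)

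- PBMT-sMF - PR: 0.75 × (lambda_PR - lambda_IPC)
- ESWT - PR: 0.75 × (lambda_PBMT-sMF - lambda_IPC)
- IPC - PR: 0.75 × (lambda_ESWT - lambda_IPC)

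One unit of lambda_IPC gives -0.75 on all three. Carryover of the same size from all four conditions gives zero.

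**3. Can carryover be separated?** Yes, poorly. The design matrix has rank 10 without carryover and 13 with it, so all treatment and carryover contrasts are estimable. On contrasts, after removing participants and periods, the information is:

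- treatment: 4
- carryover: 3 - 1/4 = 2.75
- cross term: 3 (three repeats of one fixed pairing)

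Squared canonical correlation = 3² / (4 × 2.75) = 9/11 = 0.818, so the correlation is 0.905.

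Variance of a treatment contrast:

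- unadjusted: 2/4 = 0.50 sigma²
- adjusted: 2 / (4 - 9/2.75) = 2/0.727 = 2.75 sigma²

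The ratio is 2.75/0.50 = 5.5. The standard error grows by sqrt(5.5) = 2.35.

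**4. The same steps for a Williams square** (each of the 12 ordered pairs once). Each mean carries a quarter of the residual of each of the other three interventions, so bias(i - j) = -0.25 × (lambda_i - lambda_j). One unit from an active therapy biases only its own contrast with PR, by -0.25; one unit from PR gives +0.25 on each active-versus-PR contrast. The cross term has size 1, so the adjusted variance is 2 / (4 - 1/2.75) = 2/3.636 = 0.55 sigma². That is 1.1 times 0.50, and the canonical correlation is 0.302.

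**5. Scale (assumption only).** If IPC left a residual of 0, 0.5, 1 or 2 points on the CMJ percentage change and the other conditions left none, every active-versus-PR contrast in the listed design would move by 0, -0.375, -0.75 or -1.5 points. The Protocol gives nothing from which to choose among these values.

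**The case against.** **What stands.** Each intervention is a single application of about half an hour, the last assessment is at 48 hours, and the next session is a week later. Carryover may be negligible. If each session's own pre-WOD value is the baseline, as Study Sessions suggests (the Abstract is less clear), a residual that shifts pre- and post-WOD jump height equally cancels in absolute change and mostly cancels in percentage change. The primary outcome is then at risk only from carryover that alters the response to the next WOD. The absolute post-WOD values, which are also to be analysed, do not have this protection.

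The Williams square does not remove bias, nor is it better for every contrast when carryover goes unadjusted. If all three active therapies left the same residual lambda and PR left none, the listed design would bias PBMT-sMF - PR by -0.75 lambda and leave ESWT - PR and IPC - PR unbiased. The Williams square would bias each of the three by -0.25 lambda. Its advantages are a smaller worst case, no spurious ranking among the active therapies in that scenario, and above all cheap adjustment.

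A carryover sensitivity analysis is commonly left to an SAP, so its absence here is not a fault. An SAP cannot, however, change the 5.5-fold cost, which the sequence list fixes.

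**What a reader might infer, but should not.**

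- *That carryover is fully aliased with treatment.* Each intervention is given once in session 1 with no predecessor, all contrasts remain estimable, and equal carryover cancels.
- *That the rotation makes the next intervention predictable.* In any four-sequence Latin square, the Williams square included, knowing the list and the first intervention reveals the rest. The Protocol does not say that participants or assessors are shown the list.
- *That repeating the same WOD makes matters worse.* The WOD is identical in every condition, so adaptation to it is a period effect, which the listed design already balances.

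**Conclusion.** The point holds as an avoidable design weakness. The square is balanced for period and unbalanced for first-order carryover. Differential carryover that alters the next response would be heavily confounded with treatment (correlation 0.905), with 75% of the predecessor's residual entering each unadjusted mean. Adjusting for it leaves 0.50/2.75 = 18% efficiency.

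These figures assume equal numbers per sequence, complete data, additive first-order carryover and a within-participant analysis. They describe how vulnerable the design is. The documents do not show that any carryover survives seven days, so the actual bias is unknown and may be zero. This is a should-fix improvement and does not invalidate the trial.

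**What to change.** Before randomisation, replace the list with a Williams square:

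- PR → PBMT-sMF → IPC → ESWT
- PBMT-sMF → ESWT → PR → IPC
- ESWT → IPC → PBMT-sMF → PR
- IPC → PR → ESWT → PBMT-sMF

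Each intervention occurs once per period and precedes each other intervention exactly once. Keep the equal allocation. A sensitivity analysis with a first-order carryover term then becomes affordable. The number of sequences, sessions and participants is unchanged, so the cost is a new randomisation list and new envelopes.

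If participants have already been allocated (the file ends with a reference to a dataset of individual results), the list cannot be repaired. In that case, state the imbalance as a limitation, report a carryover-adjusted sensitivity analysis with its interval about 2.35 times as wide, and make clear that a null carryover test in this design is weak reassurance.
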